#### Women’s experience study (EQUIPTT-Q)

When feasible (i.e. participants identified prior to assessment and staff available to obtain consent), participants in the cluster randomised trial will be invited to complete a questionnaire booklet. This includes questions about her symptoms, anxiety levels before and after her clinical assessment, the tests she received, her options for further management and the extent to which she is content with the decisions made. Anxiety levels and decisional conflict will be ascertained by visual analogue scale (VAS), and the Decisional Conflict Scale (DCS) questions [19]. The questionnaire booklet has been designed in collaboration with the Women’s Health Academic Centre’s Preterm Birth Studies public and patient involvement (PPI) panel. Difference in VAS anxiety scores between women before and after assessment, and between hospitals with and without QUIPP app in use at the time of assessment, will be calculated (paired and independent samples t-test). Difference between DCS scores after assessment, between hospitals with and without QUIPP app in use, will also be calculated (paired and independent samples t-tests as appropriate). If the DCS and VAS data is found to be not normally distributed, non-parametric equivalent tests will be used.

A subgroup of participants (approx. 20–30) will be invited to provide a more in-depth account of their experiences during one-to-one face-to-face or telephone interviews. The interview schedule will be determined following interim analysis of the data and free text box comments. The Framework approach [20] will be used to analyse the qualitative data obtained from the interviews. This method of qualitative data analysis is suitable for use with the anticipated findings from this study. Data will be analysed using NVivo software.

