### Sample size

For inappropriate admission decisions, a total sample size of 580, approximately 50 recruits per site, was calculated. Data from our group’s ongoing prospective observational study into the ability of qfFN to predict preterm birth in symptomatic women (PETRA REC Ref. 14/LO/1988) has allowed us to estimate the likely treatment effect for the intervention reducing inappropriate admissions from 25 to 10% and intra-class correlation 0.030. Based on 13 clusters this treatment effect requires approximately 580 for 80% power. We are aware that a larger number of centres would also be preferable, but believe 13 is adequate and at the limit of what is currently feasible.

For our qualitative questionnaires, we have estimated a target recruitment of 300 participants, 25 recruits per site, allowing for non-compliance and data collection errors. Based on previous research involving visual analogue scale (VAS) scores [19], a total sample size of 272 was required at standard levels of significance (alpha = 0.05 two-sided) to achieve 90% power to detect a 10% difference in mean VAS scores between hospitals with and without the intervention.

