For the health economics analysis data will be collected from routine medical records on antenatal admissions, length of stay, outpatient appointments, day cases and scans for women identified as participants in the trial from the time of first being identified as part of the trial until discharge following delivery. Healthcare resource group codes for each event will be collected and costs from National Reference costs applied. We will conduct a time and motion study of clinician time and resources spent identifying a suitable transfer location on a sample of transfers. We will also conduct a micro costing of the cost of a transfer. We will also collect and report statistics and costs per patient for mode of delivery for women identified as participants in the trial and ex-utero transfers and NICU stays for their neonates (adjusting for non-singleton births). We will include the cost of the intervention which will include the cost of any training and the cost of clinician time associated with using the app. This information will be collected from the app, patient notes and a time and motion questionnaire administered to clinicians for a subset of patients.

For the women’s experience study (EQUIPTT-Q) participants, following consent, the researcher will enter the woman’s initials, hospital number, date of birth and date of signing consent against the next consecutive EQUIPTT-Q ID number on the EQUIPTT-Q register. This ID number will be entered on the consent form and alternative pages of the questionnaire booklet. The participant will be asked to complete part 1 (questions regarding baseline demographics, her symptoms and anxiety levels prior to assessment) straight away. She will be asked to keep the booklet with her and to complete part 2 (tests, planned interventions, anxiety post assessment and decisional conflict scale questions) after her clinical assessment. She will then hand the completed booklet back to staff before leaving the unit. The researcher checks the booklet for completion and enters data on EQUIPTT-Q datasheet (spreadsheet). The datasheet (which contains no identifiable data) is emailed to trial management team on a weekly basis. Data will be merged into the EQUIPTT-Q SPSS database which is separate from the main trial database.

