#### Women’s experience study (EQUIPTT-Q)

Our key outcome is difference in VAS anxiety scores between women before and after assessment, between hospitals with and without QUIPP app in use at the time of assessment. We will also analyse difference between DCS scores after assessment, in hospitals with and without QUIPP app in use.

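### EQUIPTT-Q uses the pre-assessment VAS anxiety score only by subtraction; using it as a covariate would be more precise and would handle chance baseline imbalance better

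*Protocol article*

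**What the plan says.** All references are to the protocol article.

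- **Data collection.** The booklet has two parts. Part 1, completed before assessment, holds "questions regarding baseline demographics, her symptoms and anxiety levels prior to assessment". Part 2, completed afterwards, holds "tests, planned interventions, anxiety post assessment and decisional conflict scale questions". Each woman with a complete booklet therefore has a VAS anxiety score before and after.
- **Outcomes, Women's experience study.** "Our key outcome is difference in VAS anxiety scores between women before and after assessment, between hospitals with and without QUIPP app in use" when the woman is assessed. This is a change score contrasted between two groups of hospitals.
- **Data analysis, Women's experience study.** The analysis covers "Difference in VAS anxiety scores between women before and after assessment, and between hospitals with and without QUIPP app in use at the time of" the woman's assessment. The section adds that these differences "will be calculated (paired and independent samples t-test"). The natural reading is a paired test for before against after within women, and an independent-samples test between hospitals. The fallback is: "If the DCS and VAS data is found to be not normally distributed, non-parametric equivalent tests will be used". No covariate is named.
- **Sample size.** A total of 272 women is said to give "90% power to detect a 10% difference in mean VAS scores between hospitals with and without the intervention", at two-sided alpha 0.05. The section does not say whether the scores meant are post-assessment scores or changes, and it gives no SD.
- **Data analysis, Cluster randomised trial.** Adjustment for ethnicity and maternal age is mentioned here, under a separate heading. Pre-assessment VAS is not.

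**The concern.** The protocol commits to named tests that cannot take a covariate, although the strongest likely predictor of post-assessment anxiety is already in the booklet. Subtracting the baseline fixes its slope at 1. When scores before and after have equal variance, the actual slope is their correlation, which is below 1 for any realistic questionnaire score. Two things follow. Precision that the data could give is lost. And if one group of hospitals happens by chance to have more anxious women at the start, regression to the mean makes that group appear to improve more.

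Chance imbalance is plausible, because only 13 hospitals are randomised, seven to one group and six to the other. What is at stake is the precision and interpretation of the key result of the questionnaire sub-study. The trial's primary outcome is not affected.

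**Working it through.** **Inputs from the protocol (Sample size):** total N = 272, power 90%, two-sided alpha 0.05. **Not given:** the SD, and the correlation rho between scores before and after. I assume 136 women per group, equal SDs before and after, independent women, and rho from 0.3 to 0.7.

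**1. The protocol's own figure.** A two-sample t-test with 136 per group has 90% power at a standardised difference d = 0.394. If the 10% difference means 10 points on a 0-100 scale (an assumption), the implied SD is about 25.4. By the normal approximation that SD returns 272 in total, and an SD of 25 returns 264. The figure is therefore consistent with a plain comparison of two means. It cannot be confirmed, because no SD is stated.

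**2. Variance of the between-group estimate, relative to a post-score comparison**

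- post-assessment score only: 1
- change score: 2(1 − rho)
- post-assessment score adjusted for baseline: 1 − rho²

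Adjusted relative to change: (1 − rho²) / [2(1 − rho)] = (1 + rho)/2. This is below 1 for every rho below 1.

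**3. Power at N = 272 if d = 0.394 refers to a single score.** Divide d by the square root of the variance factor and use the noncentral t:

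| rho | Factor, change | Factor, adjusted | Power, post score | Power, change | Power, adjusted |
|---|---|---|---|---|---|
| 0.3 | 1.40 | 0.91 | 90.0% | 78.2% | 92.5% |
| 0.5 | 1.00 | 0.75 | 90.0% | 90.0% | 96.3% |
| 0.7 | 0.60 | 0.51 | 90.0% | 98.7% | 99.5% |

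**4. If 272 was instead sized on the SD of a change.** The change score then has 90% power at every rho. The adjusted analysis needs (1 + rho)/2 of 272 for the same power: 0.65 × 272 = 177, 0.75 × 272 = 204 and 0.85 × 272 = 231 women at rho 0.3, 0.5 and 0.7. The efficiency gain does not depend on which SD was used. The shortfall below 90% does.

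**5. Baseline imbalance of 5 points, no app effect**

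| Source of imbalance | Method | rho 0.3 | rho 0.5 | rho 0.7 |
|---|---|---|---|---|
| Chance | change, −5(1 − rho) | −3.5 | −2.5 | −1.5 |
| Chance | post score, 5·rho | +1.5 | +2.5 | +3.5 |
| Chance | adjusted | 0 | 0 | 0 |
| Stable difference between hospitals, same before and after | change | 0 | 0 | 0 |
| Stable difference between hospitals, same before and after | adjusted, 5(1 − rho) | +3.5 | +2.5 | +1.5 |

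Which method is unbiased depends on where the imbalance comes from.

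**The case against.** The strongest reply is that a change score is a recognised analysis and does use the baseline. That is right. A reader might infer that EQUIPTT-Q ignores the baseline altogether, but the Outcomes section makes the before-after difference the key outcome. The complaint is about how the baseline is used.

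A reader might also infer that covariate adjustment would cure any baseline difference between hospitals. The protocol does not support that. Women are invited only when feasible and with consent, at hospitals already allocated, so the women recruited could differ systematically. The last two rows of the second table show that in the stable case the change score is unbiased and the adjusted estimate is not. This part of the objection stands, and it is why both analyses should be reported.

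Nor can it be said that the stated 90% fails for the key outcome. It falls short only if 272 rests on a single-score SD and rho is below 0.5, and the protocol settles neither. At rho 0.7 the gain from adjustment is under one percentage point.

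Finally, one could quote much lower power by adding hospital clustering. That the t-tests ignore clustering is a separate matter. Any combined figure would need an assumed ICC and a further assumption about how far the baseline explains variation between hospitals, so none is used here.

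**Conclusion.** The point holds as a matter of efficiency and of chance imbalance. The stated tests use the pre-assessment score less well than the data allow for any correlation between 0 and 1, given equal variances. With 272 women sized on a single-score SD and treated as independent, the gain in power over the change score is 14 points at rho 0.3 (92.5 − 78.2), 6 at rho 0.5 (96.3 − 90.0) and 0.8 at rho 0.7 (99.5 − 98.7). The correlation and the SD are assumptions, so the direction is firm and the size is not.

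The documents do not show that the planned comparison is biased, or that adjustment would remove differences due to recruitment. The point concerns a sub-study outcome and is worth acting on mainly because the change costs so little.

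**What to change.** In the two Women's experience study sections (Data analysis and Outcomes):

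1. Define the key comparison as post-assessment VAS regressed on hospital group, with the woman's pre-assessment VAS as a covariate, in a model that accounts for hospital.
2. Keep the stated contrast, which is whether the app was in use at the time of assessment. If the comparison is meant to be limited to the randomised nine-month period, say so. The two can differ, because control units receive the app in the final phase (Trial design), and the article does not say which phases EQUIPTT-Q covers.
3. Replace the non-parametric fallback with one that keeps the covariate, such as bootstrap or permutation inference on the same model.
4. Report the unadjusted change-score comparison alongside as a sensitivity analysis, noting that the two methods rest on different assumptions about the source of any baseline difference.
5. In Sample size, state whether 272 rests on the SD of a single score or of a change.

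The cost is wording and a slightly longer analysis, with no new data. Women who did not complete part 1 would need simple baseline imputation to stay in the model.

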#### **Hypothesis:** The implementation of the QUIPP app and management algorithm will decrease inappropriate management for TPTL

### Trial design

EQUIPTT is a cluster randomised controlled trial (incorporating a parallel group design) across 13 obstetric centres. This design was chosen as for this scale of protocol intervention (in an emergency situation), it would be challenging to randomise at participant level, affecting uptake and generalisability of the findings, and individual clinicians cannot be randomised to varying decision-making with individual patients.

The pragmatic approach was taken to introduce the QUIPP app to entire hospital antenatal units, as standard practice for all clinicians, and all affected pregnancies. Using this parallel cluster studies have the added value of limiting the time-bias which occurs with a stepped wedge design. Also, unlike in a crossover design, the intervention does not need to be retracted from the cluster, avoiding contamination bias. Individuals within a cluster tend to have more similar outcomes than across clusters. The similarity in the outcomes of individuals within a cluster within a time period is typically measured by the within-cluster within-period intra-cluster correlation coefficient. If this is not factored into the power calculation and analysis, the effectiveness of the intervention may be exaggerated [18].

All 13 centres will provide data related to the principal outcome under their current practice in a six-week pre-intervention data collection period. Following randomisation, the centres will use intervention (using the QUiPP app) or control (routine management) for a nine-month analysis period. In the final phase of the trial, the intervention will be introduced in the 6 control units. Following this, data will be collected for a further six weeks across all 13 sites, in order to equally incentivise all sites to participate. The QUIPP app approach will be adopted as standard practice in all sites if successful. A list of the study sites is available from the authors on request.

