### Randomisation

Randomisation is at the cluster level. Centres have been randomly allocated to receive either intervention or control. Due to there being an odd number of centres, seven sites were allocated to one group and six to the other. Minimisation of the randomisation list was not appropriate for this design but the imbalances between three levels of NICU facility at intervention and control sites were small (4:3, 3:2, and 0:1). TPTL rates were known for 10 sites and the difference between the average rates at control and interventions sites were within chance (72 and 89%).

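### The EQUIPTT-Q comparisons between hospitals use t-tests or rank tests that ignore hospital-level randomisation, so at any positive ICC they are anti-conservative

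*Protocol article*

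**What the plan says.** All references are to the protocol article.

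- **Unit of randomisation.** Under Randomisation: "Randomisation is at the cluster level", and "seven sites were allocated to one group and six to the other".
- **Who is in EQUIPTT-Q.** Under Data analysis, Women's experience study: where feasible, "participants in the cluster randomised trial will be invited to complete a questionnaire booklet". The women are therefore nested in the randomised hospitals.
- **Key outcome.** Under Outcomes, Women's experience study, it is the "difference in VAS anxiety scores between women before and after assessment, between hospitals with and without QUIPP app in use at the time of assessment".
- **Tests named.** For VAS, the difference "between hospitals with and without QUIPP app in use at the time of assessment, will be calculated (paired and independent samples t-test"). For DCS after assessment, the difference between hospitals "will also be calculated (paired and independent samples t-tests as appropriate"). As a fallback: "If the DCS and VAS data is found to be not normally distributed, non-parametric equivalent tests will be used". None of these has a cluster term.
- **The article's own standard.** Trial design says of the intra-cluster correlation: "If this is not factored into the power calculation and analysis, the effectiveness of the intervention may be exaggerated". The Cluster randomised trial analysis has a random effect and cluster-adjusted standard errors, and the Health economics evaluation uses a multi-level model. Each statement sits under its own heading, and nothing extends either to EQUIPTT-Q.

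**The concern.** An independent-samples t-test, or its rank equivalent, computes its error from the spread between women. Where hospitals are allocated, the relevant error also contains the variation between hospitals. If women assessed in the same hospital respond even slightly alike, the test claims more information than 13 hospitals supply.

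Whether the app reduces women's anxiety or helps them with decisions is a stated aim (Background). That conclusion would rest on a test whose false-positive rate may exceed its label. The fault lies in the stated precision. Ignoring the clustering does not in itself bias the estimated difference.

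This is not a detail left to an analysis plan that is not shown, because the article names the tests.

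**Working it through.** **Inputs**

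- 13 hospitals, 7 v 6 (Randomisation). Degrees of freedom between hospitals: 13 − 2 = 11.
- Required N = 272, two-sided alpha 0.05, power 90%, 10% difference in mean VAS; recruitment target 300 (Sample size).
- Women per hospital: 272/13 = 20.9; 300/13 = 23.1.
- ICC for VAS or DCS: not given. Assumed range 0 to 0.05. The 0.030 under Sample size belongs to inappropriate admissions and is a reference value only.
- SD of VAS: not given. The 10% is read as 10 points on a 0–100 scale (assumption).

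**1. The stated 272**

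With no SD, 272 can only be back-solved. For two equal groups of 136 and no design effect:

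d = (1.960 + 1.282) × √(2/136) = 0.393, so SD = 10/0.393 = 25.4.

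The same formula gives 264 at SD 25 and 286 at SD 26. So 272 is consistent with a calculation without clustering and an SD near 25.4. That is not proof of how it was obtained.

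**2. True type I error of the unadjusted t-test**

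Design effect DE = 1 + (m − 1) × ICC. True two-sided error ≈ 2 × [1 − Φ(1.96/√DE)].

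Example, m = 20.9 and ICC 0.03: DE = 1 + 19.9 × 0.03 = 1.60; 1.96/√1.60 = 1.55; error ≈ 0.12.

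For 300 women (m = 23.1):

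| ICC | DE | Effective N | Type I error, formula | Type I error, simulated | Coverage of nominal 95% CI |
|---|---|---|---|---|---|
| 0 | 1.00 | 300 | 5.0% | 5.2% | 95% |
| 0.01 | 1.22 | 246 | 7.6% | 7.8% | 92.4% |
| 0.03 | 1.66 | 180 | 12.9% | 12.9% | 87.2% |
| 0.05 | 2.10 | 143 | 17.7% | 18.2% | 82.3% |

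The simulation used 20,000 null trials with 7 v 6 hospitals of 23 women. A t-test on hospital means in the same data rejected in 5.1 to 5.3% of trials throughout. A separate simulation with 21 women per hospital gave 7.8%, 12.3% and 17.1% at ICC 0.01, 0.03 and 0.05.

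Sample size also gives 25 per site, which over 13 sites is 325 rather than 300. At m = 25 the formula gives 7.8%, 13.5% and 18.6%, so the discrepancy matters little here.

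**3. Power once clustering is respected**

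For N = 300 split 6:7 over the hospitals (138.5 and 161.5 women), in SD units:

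SE = √[DE × (1/138.5 + 1/161.5)] = 0.1158 × √DE.

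Power comes from a noncentral t with 11 df and noncentrality 0.393/SE. At ICC 0.03, SE = 0.149 and the noncentrality is 2.63.

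| ICC | Power, 11 df |
|---|---|
| 0 | 87% |
| 0.01 | 80% |
| 0.03 | 67% |
| 0.05 | 57% |

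Part of the loss comes from using 11 df, which is why power is 87% even at ICC 0. A normal approximation gives 92% there.

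**4. Rank tests.** No separate calculation was made. A two-sample rank test also assumes independent women, so switching to it for non-normality leaves the fault in place.

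**The case against.** **The size is unknown.** The inflation depends on an ICC that the documents do not give. The 0.030 describes a clinician's admission decision and need not carry over to a woman's change in anxiety. A change score also removes stable hospital differences in starting anxiety. At ICC 0.005 the error is only 6.3%, and at ICC 0 the test is valid. All of this stands, so the size must be stated conditionally. It does not rescue the test: a change score does not remove hospital differences in how assessment alters anxiety, and DCS has no before-assessment value.

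**EQUIPTT-Q is a sub-study.** The primary outcome is analysed with a cluster term. This stands and limits the consequence.

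**Stronger readings that the documents do not support.**

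- *That the randomised comparison is lost.* A reader might infer this because groups are defined by the app being in use when the woman is assessed. The wording is at hospital level, and during the nine months planned app status is the allocation. No section says that EQUIPTT-Q women from other phases will be pooled, and Trial design confines the pre-intervention collection to data on the principal outcome. However, control units receive the app in the final phase, and the EQUIPTT-Q period is not stated. The wording permits pooling, so it needs clarifying.
- *That the change score is an error.* It is a valid comparison under randomisation. Covariate adjustment would usually be more precise.
- *That an impossible paired test is planned for DCS.* DCS is completed once, after assessment (Data collection), but the text asks for paired or independent tests only as appropriate. This is loose wording without effect on a result.
- *That stated confidence intervals are wrong.* The EQUIPTT-Q section promises none; the point applies to any derived from these tests.

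**Conclusion.** The point holds for the VAS and DCS comparisons between hospitals. The named tests do not fit a trial with 13 randomised hospitals, and they conflict with the article's own warning and with its other two analyses. The direction of the error is certain at any positive ICC. Its size rests on an assumed ICC, on roughly equal numbers per hospital and, for power, on the back-solved effect size.

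Even an ICC of 0.01 raises the false-positive rate by about half, from 5% to about 8%. The paired before/after test within women answers a different question and is outside this point. The analysis should be corrected before results are reported, but the trial's primary conclusion does not depend on it.

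**What to change.** 1. Replace the between-arm t-tests and rank tests for VAS and DCS with a linear mixed model: randomised allocation as the effect, a hospital random intercept and small-sample inference on about 11 df. A t-test or permutation test on hospital means is an acceptable alternative. The permutation test can also replace the rank tests as the fallback for non-normal data.
2. Group women by their hospital's randomised allocation, and state that the comparison is limited to the nine-month randomised period.
3. Optionally, model after-assessment VAS with before-assessment VAS as a covariate. This gains precision and does not correct an error.
4. Keep the paired t-test only as a description of before/after VAS change.
5. Under Sample size, state the SD and the assumed ICC behind the EQUIPTT-Q figure, and restate power over a range of ICCs.

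**Cost.** No new data are needed. Intervals will be wider, and the 90% power will not stand: for 300 women it is about 80% at ICC 0.01 and 67% at 0.03. Limiting the period could reduce numbers if recruitment was meant to extend beyond it.
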